### **2.8.4 Withdrawals and losses to follow-up**

The reasons for withdrawal from the trial will be summarised overall and by treatment arm if available.

In addition to describing the number of participants withdrawing and/or lost to follow-up (i.e., not returning for subsequent assessments) between pre-screening and baseline home assessments, withdrawals and/or losses to follow-up will also be described for the time periods:

- Between randomisation and weekday activity diary in week 4
- Between the weekday activity diary in week 4 and the follow-up Lab visit

## **2.9 *Pre-processing of actigraphy and eye-tracking data***

### **2.9.1 Actigraphy data**

Pre-processing of Actigraphy data will be done in the CamNtech MotionWare Software. The following data will be excluded before analysis:

- Periods of non-wear will be excluded using the MotionWare algorithm and parent-reported Actigraph removal on the Sleep Diary.
- Periods of external movement (e.g. car/buggy) will be excluded using the parent-reported Sleep Diary.

Actigraphy sleep analysis will be conducted using the CamNtech MotionWare software to deduce our primary and secondary sleep metrics. Daytime nap data will be excluded if any of the following are observed:

- A period of non-wear was reported during the nap period
- A period of external movement was reported during the nap period
- The parent reported that the child's day was not typical (e.g. child illness, child sleeping in different location, disturbance) using the parent-reported Sleep Diary.

Night time sleep data will be excluded if any of the following are observed:

- A period of non-wear was reported during the sleep period
- A period of external movement was reported during the sleep period
- The parent reported that the child's night was not typical (e.g. child illness, child sleeping in different location, disturbance) using the parent-reported Sleep Diary.
- The sleep period occurred on Daylight Saving Time (e.g. 30/10/2022)

Actigraph data for each participant will be excluded from all analysis if there are < 3 days day or night data, respectively for nap or sleep analysis.

## **2.9.2 Eye-tracking data**

### **2.9.2.1 Visual Search Task**

A Trial in the Visual Search Task will be classed as valid if:

- A saccade towards the central fixation is made, followed by a saccade towards the target apple within 4000ms of the search array presentation.

A trial in the Visual Search Task will be classed as invalid if:

- No saccade towards the central fixation is made. Trials where no saccade towards the central fixation is made are recycled.
- No saccade towards the target is made.

The Visual Search Task per participant will be excluded if there are less than 5 valid trials. Trials will be classified into Single Search and Conjunction Search based on stimulus presentation. Reaction times for valid trials in the Single Search condition will be averaged to create our Single Search saccadic reaction time secondary outcome variable.

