### **2.9.2.2 Anti-Saccade Task**

A trial in the Anti-Saccade Task will be classed as valid if:

- A saccade towards the distractor was made within 400ms of its presentation and the target was not fixated. This trial is labelled as a Pro-Saccade.
- A saccade towards the distractor was made within 400ms of its presentation and an anticipatory saccade to the target before or within 100ms of it being presented. This trial is labelled as a Corrective-Saccade.
- No saccade towards the distractor was made and a saccade to the target was made before or within 100ms of it being presented. This trial is labelled as an Anti-Saccade.
- A saccade towards the distractor was made within 400ms of its presentation and then a saccade was made towards the target > 100ms after it was presented. This trial is labelled as Pro-Saccade Reactive.

A trial in the Anti-Saccade Task will be classed as invalid if:

- No saccade towards the distractor is made and a saccade towards the target is made after it was presented (>100ms after the target presentation).
- The distractor was fixated between 400 and 1000ms after it was presented and the target was not fixated.

- The distractor was fixated between 400 and 1000ms after it was presented and an anticipatory saccade to the target was made ( $\leq$  100ms after the target presentation).
- The distractor was fixated between 400 and 1000ms after it was presented and the target was fixated after it was presented ( $>$  100ms after the target presentation).
- No distractor saccade or target saccade is made. Trials where no saccade was made are recycled.

The Anti-Saccade Task per participant will be excluded if there are less than 5 valid trials. Reaction times for valid Pro-Saccade and Pro-Saccade Reactive trials will be averaged to create our Pro-Saccade saccadic reaction time secondary outcome variable. The number of valid Anti-Saccades will be divided by the total valid trials and multiplied by 100 to create our proportion of Anti-Saccades secondary outcome variable.

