#### 2.9.2.3 Gap-Overlap Task

A trial in the Gap-Overlap Task will be classed as valid if:

- A saccade towards the central fixation was made, followed by a saccade towards the target peripheral stimulus within 2500ms of the peripheral target being presented.

A trial in the Gap-Overlap Task will be classed as invalid if:

- The target peripheral stimulus is presented on the vertical axis.
- No saccade towards the central fixation is made. Trials where no saccade towards the central fixation is made are recycled.
- No saccade towards the target peripheral stimulus is made.
- A saccade toward the wrong side of the screen is made.

The Gap-Overlap Task per participant will be excluded if there are less than 5 valid trials. Trials will be classified into Baseline, Gap and Overlap Trials based on stimulus presentation. Reaction times for valid Baseline trials will be averaged to compute our Baseline saccadic reaction time secondary outcome variable. Reaction times for valid Overlap trials will be averaged to compute an Overlap saccadic reaction time variable. Baseline saccadic reaction times will be subtracted from Overlap saccadic reaction times to compute our Disengagement saccadic reaction time secondary outcome variable.

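### In Visual Search and Gap-Overlap the minimum of 5 valid trials is counted over the whole task, not over the stimulus conditions that form each reaction-time outcome

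*SAP*

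**What the plan says.** The SAP sets one exclusion rule per eye-tracking task.

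- **Visual Search (2.9.2.1).** A trial is valid when this holds: "A saccade towards the central fixation is made, followed by a saccade towards the target apple within 4000ms of the search array presentation". That definition does not mention condition. The exclusion rule is "The Visual Search Task per participant will be excluded if there are less than 5 valid trials". The split comes only afterwards: "Trials will be classified into Single Search and Conjunction Search based on stimulus presentation". The outcome then uses one of the two conditions: "Reaction times for valid trials in the Single Search condition will be averaged to create our Single Search saccadic reaction time secondary outcome variable".
- **Gap-Overlap (2.9.2.3).** The order is the same: "The Gap-Overlap Task per participant will be excluded if there are less than 5 valid trials", then "Trials will be classified into Baseline, Gap and Overlap Trials based on stimulus presentation". Baseline reaction time uses Baseline trials only. For disengagement, "Baseline saccadic reaction times will be subtracted from Overlap saccadic reaction times to compute our Disengagement saccadic reaction time secondary outcome variable". Gap trials count towards the 5 but enter neither outcome.
- **Anti-Saccade (2.9.2.2).** The rule has the same form: "The Anti-Saccade Task per participant will be excluded if there are less than 5 valid trials". Here the four labels describe what the child did, not what was shown.

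The SAP states no minimum per condition. Section 2.8.3, whose title covers lab as well as actigraphy measures, gives a rule for actigraphy only. Section 2.9.1 does tie its minimum to the outcome: the 3-day requirement applies to day data for naps and to night data for sleep.

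**The concern.** A minimum trial count is there to keep out reaction-time means that rest on too little data. Counted over the whole task, it does not do so. A child with 5 valid Conjunction trials and no Single Search trial passes. So does a child with 1 Baseline, 1 Overlap and 3 Gap trials, whose disengagement score is the difference between two single trials.

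The point matters most for Single Search reaction time. Section 1.1.1 names it as one of two outcomes whose mean and SD are to be estimated for powering the confirmatory trial. Noise from very short averages adds to that SD. Baseline values of the outcomes are also covariates in the regression of section 2.6.2.1, so the noise can enter on both sides of the model.

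**Working it through.** The SAP derives no figure here, so there is nothing to reproduce. The check asks which trial counts pass the rule and how imprecise the resulting values can be.

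**Inputs.** From the SAP: a threshold of 5 valid trials per task; 2 Visual Search conditions, 1 contributing; 3 Gap-Overlap conditions, 1 contributing to Baseline and 2 to disengagement. Assumed, because the SAP gives no trial numbers: valid trials fall independently into conditions, with equal shares unless stated.

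**1. Visual Search.** The number of Single Search trials among n valid trials is Bin(n, p).
- n = 5, p = 0.5: every count from 0 to 5 passes. P(0) = 1/32 = 3.1%. P(at most 1) = 6/32 = 18.8%.
- n = 10, p = 0.5: P(at most 1) = 11/1024 = 1.1%.
- If the Single Search share runs from 0.75 to 0.25, P(at most 1) runs from 1.6% to 63.3% at n = 5, and from under 0.01% to 24.4% at n = 10.

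**2. Gap-Overlap.** Shares are 1/3 each. P(no Baseline or no Overlap) = 2(2/3)^n − (1/3)^n.
- n = 5: 63/243 = 25.9%. n = 10: 2047/59049 = 3.5%. n = 15: 0.5%.
- P(at most 1 trial in at least one of the two): 193/243 = 79.4% at n = 5, 20.6% at n = 10, 3.9% at n = 15.

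**3. Precision of one child's value.** Let s be the trial-to-trial SD within a child. The SE of a mean of k trials is s/√k: 1.00s for 1 trial, 0.45s for 5. The SE of a difference is s√(1/k1 + 1/k2): 1.41s for 1 + 1 trials, 0.63s for 5 + 5.

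**4. Effect on the SD between children.** With r the ratio of within-child to between-child SD, the observed SD is √(1 + r²/k) times the between-child SD if every child has k trials.

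| r (assumed) | k = 1 | k = 5 |
|---|---|---|
| 0.5 | 1.12 | 1.02 |
| 1 | 1.41 | 1.10 |
| 2 | 2.24 | 1.34 |

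These are limits, since only some children would have one trial. For example, with r = 1, 10% of children on 1 trial and the rest on 5 (assumption), the variance is 1 + 0.1 × 1 + 0.9 × 0.2 = 1.28, against 1.20 with 5 trials for all. The ratio is 1.28/1.20 = 1.07, so a sample size based on it would be about 7% larger.

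**5. Cost of requiring 5 per condition.** Under the same equal-share assumption:
- Single Search, 10 valid trials: P(fewer than 5) = 386/1024 = 38%.
- Disengagement, 10 valid trials: only the split 5 Baseline, 5 Overlap, 0 Gap passes, so the loss is 1 − 252/59049 = 99.6%. With 15 valid trials it is 72%.

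**The case against.** Four objections carry weight.

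- **Frequency.** A reader might infer that a sizeable share of children will have outcomes resting on one trial. The SAP does not support that. The larger percentages describe children exactly at the threshold and fall quickly with more valid trials. Visual Search and Gap-Overlap trials without a central fixation are also recycled, which may raise valid counts. What stands is that the rule permits such values, not that they are common.
- **An outcome resting on no trials.** With no contributing trial there is no mean, so the value is missing. Section 2.8.1 already has missing data reported for each outcome measure by arm. That would show these children, but not those whose value comes from one or two trials.
- **The obvious repair.** It is tempting to move the 5 to each condition and expect to lose only a few children. Step 5 shows that the loss could be large, and the SAP gives no trial numbers to rule this out.
- **Pro-Saccade reaction time.** The same repair might seem to apply, since only two of the four valid labels contribute. But those labels are the child's own responses. A minimum would remove children who make many antisaccades, and the antisaccade proportion is itself an outcome (section 1.9.2, item 5b). At follow-up that is selection on performance after randomisation.

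It can also be said that effects are estimated without p-values or inferential claims (section 2.6.2.1). That limits the harm to the arm comparisons, but not to the SD, whose estimation is a primary objective. The protocol, not seen here, might set a minimum per condition. However, section 2.9.2 gives complete validity, exclusion and derivation rules of its own and does not defer to it.

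**Conclusion.** The point holds for the stimulus-defined outcomes: Single Search, Baseline and Disengagement reaction times. Followed as written, the rule admits values from a single contributing trial and passes children whose outcome cannot be computed. That follows from the text and needs no assumption.

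The size does rest on assumptions: independent allocation, equal shares and an unknown number of valid trials. The problem could be negligible if most children give 15 or more valid trials, and material if many are near 5. The antisaccade proportion is unaffected, because its denominator is all valid trials. The change should be made, but the documents do not show that results would be seriously distorted without it.

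**What to change.** In sections 2.9.2.1 and 2.9.2.3, apply the minimum to the valid trials of the condition or conditions that form each outcome:

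- Single Search reaction time: valid Single Search trials.
- Baseline reaction time: valid Baseline trials.
- Disengagement: valid Baseline trials and valid Overlap trials, each meeting the minimum.

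Set the number before unblinding, from the number of trials presented per condition, and state that number in the SAP. Report by arm the distribution of contributing trials and how many children lose each outcome. For Pro-Saccade reaction time, report the number of contributing trials and set no exclusion rule on it.

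The cost is a few sentences in the SAP and a change to the processing script. The downside is that some children lose an outcome, possibly many if 5 per condition is kept and few trials are presented. A lower minimum per condition may then be the better choice.

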### **2.9.2.2 Anti-Saccade Task**

A trial in the Anti-Saccade Task will be classed as valid if:

- A saccade towards the distractor was made within 400ms of its presentation and the target was not fixated. This trial is labelled as a Pro-Saccade.
- A saccade towards the distractor was made within 400ms of its presentation and an anticipatory saccade to the target before or within 100ms of it being presented. This trial is labelled as a Corrective-Saccade.
- No saccade towards the distractor was made and a saccade to the target was made before or within 100ms of it being presented. This trial is labelled as an Anti-Saccade.
- A saccade towards the distractor was made within 400ms of its presentation and then a saccade was made towards the target > 100ms after it was presented. This trial is labelled as Pro-Saccade Reactive.

A trial in the Anti-Saccade Task will be classed as invalid if:

- No saccade towards the distractor is made and a saccade towards the target is made after it was presented (>100ms after the target presentation).
- The distractor was fixated between 400 and 1000ms after it was presented and the target was not fixated.

- The distractor was fixated between 400 and 1000ms after it was presented and an anticipatory saccade to the target was made ( $\leq$  100ms after the target presentation).
- The distractor was fixated between 400 and 1000ms after it was presented and the target was fixated after it was presented ( $>$  100ms after the target presentation).
- No distractor saccade or target saccade is made. Trials where no saccade was made are recycled.

The Anti-Saccade Task per participant will be excluded if there are less than 5 valid trials. Reaction times for valid Pro-Saccade and Pro-Saccade Reactive trials will be averaged to create our Pro-Saccade saccadic reaction time secondary outcome variable. The number of valid Anti-Saccades will be divided by the total valid trials and multiplied by 100 to create our proportion of Anti-Saccades secondary outcome variable.

#### 2.9.2.3 Gap-Overlap Task

A trial in the Gap-Overlap Task will be classed as valid if:

- A saccade towards the central fixation was made, followed by a saccade towards the target peripheral stimulus within 2500ms of the peripheral target being presented.

A trial in the Gap-Overlap Task will be classed as invalid if:

- The target peripheral stimulus is presented on the vertical axis.
- No saccade towards the central fixation is made. Trials where no saccade towards the central fixation is made are recycled.
- No saccade towards the target peripheral stimulus is made.
- A saccade toward the wrong side of the screen is made.

The Gap-Overlap Task per participant will be excluded if there are less than 5 valid trials. Trials will be classified into Baseline, Gap and Overlap Trials based on stimulus presentation. Reaction times for valid Baseline trials will be averaged to compute our Baseline saccadic reaction time secondary outcome variable. Reaction times for valid Overlap trials will be averaged to compute an Overlap saccadic reaction time variable. Baseline saccadic reaction times will be subtracted from Overlap saccadic reaction times to compute our Disengagement saccadic reaction time secondary outcome variable.

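### Visual Search, Gap-Overlap and prosaccade reaction times have an upper latency limit but no lower one, so saccades at or below 100 ms would be averaged in as reaction times

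*SAP*

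**What the plan says.** Section 2.9.2 lists, task by task, what makes an eye-tracking trial valid or invalid.

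- **Visual Search (2.9.2.1).** A trial counts if central fixation is "followed by a saccade towards the target apple within 4000ms of the search array presentation". On the target saccade, the only ground for invalidity is "No saccade towards the target is made". The outcome is then formed directly: "Reaction times for valid trials in the Single Search condition will be averaged to create our Single Search saccadic reaction time secondary outcome variable".
- **Gap-Overlap (2.9.2.3).** A trial counts if central fixation is "followed by a saccade towards the target peripheral stimulus within 2500ms of the peripheral target being presented". The invalid list removes vertical-axis targets, trials with no central or target saccade, and trials where "A saccade toward the wrong side of the screen is made". Then "Reaction times for valid Baseline trials will be averaged to compute our Baseline saccadic reaction time secondary outcome variable", Overlap is averaged likewise, and "Baseline saccadic reaction times will be subtracted from Overlap saccadic reaction times to compute our Disengagement saccadic reaction time secondary outcome variable".
- **Anti-Saccade (2.9.2.2).** The plan separates "an anticipatory saccade to the target before or within 100ms of it being presented" from a target saccade more than 100 ms after presentation, which it labels reactive. Prosaccade reaction time averages the Pro-Saccade and Pro-Saccade Reactive trials. Their distractor saccade must fall within 400 ms, with no minimum.

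Section 1.7 says eye-tracking data are processed as the protocol describes. Sections 2.13 and 2.14 provide for range and validity checks but name no latency limit.

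**The concern.** An analyst who applies the lists as written keeps a target saccade at, say, 50 ms and averages it as a reaction time. The same plan, in the neighbouring task, treats a target saccade that early as anticipation of the target and not a reaction to it.

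In Gap-Overlap the filter also works one way. Early looks to the wrong side are discarded, while early looks that happen to go to the correct side stay in.

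Four secondary outcomes in section 1.9.2 are affected: Single Search (outcome 2), prosaccade (5a), Gap-Overlap Baseline (5c) and Disengagement (5d). Single Search matters most for planning. Section 1.1.1 names it as one of two outcomes whose means and SDs the trial is to supply for powering the definitive trial. Randomisation protects a comparison between arms, but it does not correct a distorted mean or SD.

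**Working it through.** The SAP has no figure to reproduce here, so the check is a comparison of the rules followed by an illustration of scale.

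**1. Rules side by side**

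| Task | Upper limit | Lower limit | Treatment of a saccade at or below 100 ms |
|---|---|---|---|
| Visual Search, target | 4000 ms | none | valid, averaged |
| Gap-Overlap, target | 2500 ms | none | valid if to the correct side, averaged |
| Anti-Saccade, distractor (for prosaccade reaction time) | 400 ms | none | valid, averaged |
| Anti-Saccade, target | – | 100 ms divides anticipatory from reactive | classified as anticipatory |

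**2. Inputs for scale.** The SAP gives no mean latency, trial count or frequency of early saccades. Assumed values: an early saccade at a = 50 ms; true mean m of 250–400 ms for Gap-Overlap and 500–1200 ms for Visual Search; n averaged trials.

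**3. One early trial among n.** Shift in the child's mean = (a − m)/n.

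- Gap-Overlap, m = 300: (50 − 300)/5 = −50 ms; with n = 10, −25 ms; with n = 20, −12.5 ms.
- Gap-Overlap, m = 250 to 400: −40 to −70 ms at n = 5; −10 to −17.5 ms at n = 20.
- Visual Search, m = 800: (50 − 800)/5 = −150 ms; with n = 20, −37.5 ms.
- Visual Search, m = 500 to 1200: −90 to −230 ms at n = 5; −22.5 to −57.5 ms at n = 20.

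The minimum of 5 valid trials applies to the whole task, not to each averaged condition, so n = 5 is not a floor for a Baseline or Single Search mean. With n = 2 and m = 300 the shift is (50 − 300)/2 = −125 ms.

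**4. A share f of early trials.** Shift = −f(m − 50). At f = 5%: −12.5 ms (m = 300), −17.5 ms (m = 400), −37.5 ms (m = 800).

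**5. Disengagement.** Assume Baseline 300 ms and Overlap 450 ms, so the true value is 150 ms. Observed = [(1 − fO)·450 + fO·50] − [(1 − fB)·300 + fB·50], where fO and fB are the early shares in Overlap and Baseline.

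| fB | fO | Overlap | Baseline | Observed |
|---|---|---|---|---|
| 10% | 10% | 410 | 275 | 135 ms |
| 10% | 0% | 450 | 275 | 175 ms |
| 5% | 10% | 410 | 287.5 | 122.5 ms |

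The error can go either way, depending on which condition holds the early saccades.

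**6. Difference between arms.** If f and a are equal in all arms, a true difference d becomes (1 − f)d. At f = 5%, 20 ms becomes 0.95 × 20 = 19 ms.

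**The case against.** The strongest reply is that the Anti-Saccade Task supplies no exclusion rule to copy. An early target look there is valid. Without a distractor saccade it is an Anti-Saccade, and after a prompt one it is a Corrective-Saccade. With no distractor saccade, it is the later target saccade that makes the trial invalid. This stands, and it rules out the reading that the plan contradicts itself or calls early looks guesses. What remains is that the plan draws a line between anticipating and reacting at 100 ms, then ignores it when it computes reaction times. Carrying that line over to distractor saccades is an extension, since the plan draws it for target saccades.

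Second, the protocol may hold a minimum latency, because section 1.7 refers processing to it. That is possible. But section 2.9.2 sets out its own lists, and those admit the trials; if the protocol differs, the two need aligning.

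Third, the size is assumed throughout. This also stands. Early hits are probably rarer in Visual Search, where the look must land on the target within an array, so the largest shifts shown belong to the task where they are least likely.

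Fourth, the stakes are limited. Section 2.6.2.1 reports no p-values and draws no inference from the effect estimates, and no traffic-light metric uses reaction time. This bears on severity but not on the planning parameters.

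**Conclusion.** The point holds as an omission with inconsistent handling, and it should be corrected before analysis. As written, saccades at or below 100 ms would be averaged into Single Search, Baseline, Overlap (and so Disengagement) and prosaccade reaction times. Each such trial pulls a child's mean down, by 40–70 ms for one in five Gap-Overlap trials under the assumed means, and Disengagement can move either way.

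A reader might go further and infer that the SD for sizing the definitive trial is inflated by a material amount. The SAP gives no basis for this: how often early saccades occur is not stated, and no SD has been calculated. Nor does the SAP support a claim that the comparison between arms is biased in a particular direction. With equal contamination a difference only shrinks slightly, and nothing indicates that contamination differs by arm.

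**What to change.** - In 2.9.2.1 and 2.9.2.3, add to the invalid criteria: *saccade to the target at or below 100 ms after target (or array) onset*. Using at or below, and not strictly below, matches the boundary in 2.9.2.2.
- In 2.9.2.2, exclude distractor saccades at or below 100 ms from the prosaccade reaction-time average only. Leave the Anti-Saccade and Corrective-Saccade classification unchanged, so that the proportion of antisaccades is not altered.
- If the protocol already sets a minimum latency, align the SAP with it.

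The cost is a few words and one filter in the eye-tracking processing. A few trials will be lost, and a few more children may fall below 5 valid trials. Settling the rule now avoids choosing a cut-off after the data have been seen.
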